#### Subgroup analysis

The duration of the cooling intervention was reduced from 24 hours to 12 hours after the recruitment of 50 participants. To investigate this protocol change, we will conduct a subgroup analysis for the primary and secondary outcomes. In the analysis, we will compare the participants who were included before the protocol change to participants included after the protocol change.

#### Sensitivity analyses

The analyses of the primary and secondary outcomes will be repeated using the per protocol population and the ‘learning curve’ population.

### Analysis of the primary and the secondary outcome

#### The primary outcome

The primary efficacy variable, the score on the mRS at the outcome assessment (day 91 ± 14 days), will be determined with ordinal (with more than two categories) logistic regression. The assumption about proportional odds will be accepted if the difference between the frequency in group 1 and that of group 2 in the various categories are all positive and different from 0 or are all negative and different from 0. If the assumption of the ordinal regression analysis model is not fulfilled, the groups will be compared using a non-parametric method (van Elteren and stratification by nationality of centre) and the result will be the primary result. If the assumption of the model is fulfilled, the result of the adjusted analysis will be the primary result.

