### Adjusting variables

The randomisation is stratified according to the nationality of the participating centres and, within each stratum, the patient allocation is based on probabilistic minimisation (80:20) using the following factors:Intention to perform thrombolysis (yes compared to no).Method of cooling (surface compared to endovascular).Sex (male compared to female).Stroke severity (National Institutes of Health Stroke Score (NIHSS)) 6–12 compared to 13 or higher).Age (≤ 65 years compared to > 65 years).Visibility of a relevant ischaemic lesion on the first brain imaging (yes compared to no).Time since symptom onset (≤ 4 hours compared to 4–6 hours).

The primary analyses will be adjusted by the protocol-specified stratification variable country and the seven minimisation factors.

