#### The primary outcome

The primary outcome is degree of disability post stroke as measured by the seven-level modified Rankin Scale measured in the period 91 ± 14 days after the patient’s randomisation.

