### Statistical analyses

#### Analytical principles

Analyses will be conducted according to the intention-to-treat principle [2] if not otherwise stated.

All primary tests of significance will be two-sided with alpha = 5%. Analyses will be conducted blinded with the two intervention groups coded as, e.g. 0 and 1. Two conclusions will be drawn, one assuming 0 is the intervention group and 1 is the control, and one assuming the opposite. After two abstracts with two conclusions have been written and both accepted by the Steering Group, the code will be broken.

The primary analyses of primary, secondary, and exploratory outcomes will be those of the intention-to-treat population adjusted for the protocol-specified stratification variable and the minimisation variables, and if necessary using data sets generated using multiple imputation.

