#### Power of the original secondary outcomes

As the sample size is based on the primary outcome, we have calculated the power of each of the originally planned secondary outcomes given the sample size of 800 patients.

Death day 91 ± 14 days after randomisation: the implied clinically relevant minimal change in mortality that needs to be detected may be calculated based on (1) the mortality of 17% found in the meta-analysis quoted in the protocol [1]; (2) the assumption that wherever the mRS is dichotomised, the odds ratio for treatment versus control will be the same, the ‘common odds ratio’; and (3) the requirement that this common odds ratio should not be larger than 0.74 (see the sample size calculation). Let the unknown change in mortality in the experimental group be x. If we assume the OR for the dichotomy mRS > 5 compared to mRS ≤ 5 will be 0.74 and the mortality of the control group is 17% as quoted in the meta-analysis, we may find x by solving the equation OR = ((0.17–x)/(0.83 + x))/(0.17/0.83) = 0.74 to obtain x = 0.0384 giving a mortality of 0.1700 – 0.0384 = 0.1316 in the cooled patients versus 0.1700 in the controls. Using a sample size of 800 participants, the power is found to be 0.33.

Death or dependency (mRS > 2) 91 ± 14 days after randomisation: using the same reasoning, the power of this outcome can be calculated by solving the equation (0.63–x)/(0.37 + x))/0.63/0.37 = (0.63 – x)0.63/(0.37 + x)0.37 = 0.74 as 63% of the patients in the meta-analysis had mRS > 2 implying x = 0.0725. The power may then be calculated to be 0.55.

NIHSS score 91 ± 14 days after randomisation: assuming a minimal relevant difference of 2 points, a standard deviation (SD) of 5 points [5], an α of 0.05, and a sample size of 800 participants, the power may then be calculated to 1.00.

EQ-5D-5 L score 91 ± 14 days after randomisation: assuming a minimal relevant difference of 0.05 points, a SD of 0.40 points [6–9], an α of 0.05, and a sample size of 800 participants, the power may then be calculated to 0.42.

WHODAS 2.0 score 91 ± 14 days after randomisation: we originally planned to analyse the World Health Organization Disability Assessment Schedule II (WHODAS 2.0) score at outcome assessment in the period day 91 ± 14 days after randomisation. However, due to difficulties in assessing the clinical meaning, we are not able to calculate the power, and we will thus analyse this as an exploratory outcome.

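### The rule for accepting proportional odds cannot be met, so the primary result always defaults to a van Elteren test that omits the seven minimisation factors and yields no common odds ratio

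*SAP article*

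**What the plan says.** The outcome is the "seven-level modified Rankin Scale", analysed by ordinal logistic regression. Under Analysis of the primary and the secondary outcome, proportional odds is accepted on this condition: "difference between the frequency in group 1 and that of group 2 in the various categories are all positive and different from 0". A second branch admits the opposite sign throughout: "or are all negative and different from 0". When neither branch is met, "the groups will be compared using a non-parametric method (van Elteren and stratification by nationality of centre) and the result will be the primary result". The adjusted ordinal model supplies the primary result only when the rule is met.

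Elsewhere the article describes a different primary analysis. The section Adjusting variables states: "The primary analyses will be adjusted by the protocol-specified stratification variable country and the seven minimisation factors". Analytical principles says the same for the intention-to-treat analyses. Table 3 is laid out for a common odds ratio with 95% confidence interval and a P value. No other section gives a different acceptance rule or says that cumulative frequencies are meant.

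**The concern.** The rule compares the arms category by category. If one arm has relatively more patients in some mRS categories, it must have fewer in others. A treatment that shifts patients towards better scores raises the frequencies at the good end and lowers them at the bad end. That is the pattern a proportional-odds effect produces, and the rule rejects it.

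At stake is which test decides the trial. Under Multiplicity, the primary outcome is tested first and testing stops at the first non-significant result, so this choice also governs whether any secondary outcome can be claimed. If the fallback always applies, the deciding test ignores the seven minimisation factors and has no odds ratio of its own. It also gives up the precision of covariate adjustment in a trial already cut from 1500 to 800 patients.

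**Working it through.** **Inputs.** From the article: seven mRS levels; control mortality 17% and control mRS > 2 of 63% (Power of the original secondary outcomes); the requirement that "this common odds ratio should not be larger than 0.74"; N = 800; two-sided alpha of 5%. Assumed: 400 per arm, and how the 37% with mRS 0-2 and the 46% with mRS 3-5 divide among their levels.

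**Input check.** Solving for an odds ratio of 0.74:
- Death: odds 0.74 × 0.17/0.83 = 0.1516, risk 0.1316, x = 0.0384, power 0.329 (article: 0.33).
- mRS > 2: odds 0.74 × 0.63/0.37 = 1.26, risk 0.5575, x = 0.0725, power 0.551 (article: 0.55).

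Both agree with the article.

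**The rule as written.** Let p1k and p2k be the proportions in category k. Then Σ(p1k − p2k) = 1 − 1 = 0. Seven non-zero numbers that sum to 0 cannot all be positive or all be negative. The rule was met in 0 of 100,000 simulated trials in every setting.

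Example with exact proportional odds, odds ratio 0.74, control split evenly within mRS 0-2 and within mRS 3-5:

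| mRS | 0 | 1 | 2 | 3 | 4 | 5 | 6 |
|---|---|---|---|---|---|---|---|
| cooled − control | +0.0364 | +0.0237 | +0.0124 | +0.0016 | −0.0119 | −0.0237 | −0.0384 |

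The positive terms add to 0.0741 and the negative ones to −0.0740, equal apart from rounding.

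**Read as raw counts.** With 400/400 the count differences also sum to 0, so the rule is impossible. It was met in at most 0.02% of trials at 410/390, 0.1-1.4% at 420/380 and 5-27% at 440/360. Any pass reflects unequal arm sizes, not proportional odds.

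**Read on the six cumulative cut-points.** The rule can then be met. With 400 per arm and proportional odds exactly true:

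| True odds ratio | Rule met |
|---|---|
| 1.00 | about 23-28% |
| 0.74 | about 77-84% |

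The ranges cover several assumed splits. With control mRS 7/14/16/17/19/10/17% the figures are 23% and 77%. With that split at 0.74, if being different from 0 means statistically different, the rule is met in 5%.

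The assumption is equally true in both rows, so the rule responds to the size of the effect. It also accepts gross violations. Assumed cut-point odds ratios of 0.95, 0.90, 0.80, 0.50, 0.40 and 0.30 give differences in P(mRS > k) of −0.003, −0.018, −0.053, −0.163, −0.145 and −0.112, which share one sign.

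**Cost in power.** A closed-form check for an unadjusted ordinal comparison at odds ratio 0.74, using the even split: V = (800/12)(1 − Σp̄k³), where p̄k is the mean of the two arms' proportions. Σp̄k³ = 0.0206, so V = 65.3. Then |ln 0.74| × √65.3 = 0.301 × 8.08 = 2.43, and power = Φ(2.43 − 1.96) = 0.68.

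Simulations with 12 countries and assumed latent R² for the baseline covariates gave:

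| Set-up | van Elteren | Adjusted |
|---|---|---|
| NIHSS and age prognostic, R² 0.14-0.30 | 0.68 | 0.74-0.78 |
| One continuous score, R² 0.14 | 0.67 | 0.75 |
| One continuous score, R² 0.30 | 0.62 | 0.82 |
| Two binary covariates, R² 0.14 (rank-regression proxy) | 0.65 | 0.72 |
| Two binary covariates, R² 0.30 (rank-regression proxy) | 0.64 | 0.79 |

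**The case against.** The authors may well have meant cumulative frequencies. The power section assumes one odds ratio at every dichotomy of the mRS, and a check that all dichotomies move the same way is its natural companion. On that reading the adjusted model would usually be primary at the design effect. The text does not say this, however, and such a check examines the direction of the shift rather than the equality of odds ratios.

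The harms also differ by reading. Taken literally, van Elteren is always primary. That is a fixed, valid test, and the loss is efficiency and the form of the estimate. Taken cumulatively, the test is chosen from outcome data by arm. A simulation of that switching procedure (same two-binary-covariate set-up) showed no inflation: type I error was 0.047 at R² 0.14 and 0.043 at R² 0.30, with power 0.70 and 0.73. So this write-up makes no claim of excess false positives.

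Two qualifications stand. Table 3 is unconditional, so a common odds ratio may still be printed; it would come from a different method than the primary P value. And the fallback can be seen as a stated exception to the general adjustment rule; the conflict arises because the exception always applies.

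**Conclusion.** The rule is wrong as written. For proportions, and for counts in equal arms, it cannot be met whatever the data, and this needs no assumption about the mRS distribution. The ordinal model promised as the primary analysis could then never be the primary result, and the country-only van Elteren test would take its place. The cumulative reading makes the rule attainable but does not make it a check of proportional odds. Two analysts reading the sentence differently could report different primary results from the same data.

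The acceptance rates rest on 400 per arm and assumed mRS splits. The power gap, roughly 0.06 to 0.20, rests further on the assumed R² and number of countries and is illustrative. Dichotomised covariates, as in the minimisation, could narrow it.

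**What to change.** Delete the acceptance rule and the switch. State that the proportional-odds model adjusted for country and the seven minimisation factors is the primary analysis unconditionally, with the common odds ratio interpreted as an average shift across the cut-points. Report the six cumulative odds ratios and a score or Brant test descriptively, with no bearing on which result is primary. Keep the van Elteren test, or a covariate-adjusted win odds, as a sensitivity analysis.

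Replacing the rule by a correctly worded criterion would remove the impossibility, but the primary test would still be chosen from the data and the fallback would still lack the minimisation factors. The unconditional model matches what Adjusting variables and Table 3 already promise.

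The cost is SAP wording only. It needs no new data and must be done before unblinding.

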#### The secondary and the exploratory outcomes

Frequencies and percentages per group as well as risk ratios with 95% confidence interval (CI) will be reported for binary outcomes. Continuous variables and rate variables will be summarised using mean, standard deviation, 25, 50 and 75 percentiles, and minimum and maximum values.

Logistic regression for binary quantities, the general linear univariate model for continuous outcomes, and the Poisson distribution or negative binomial distribution for rate outcomes will be used. If the assumptions of the Poisson or negative binomial models are not fulfilled with reasonable approximation, a non-parametric method (van Elteren adjusted by nationality of centre) will be used.

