No adjustment for nationality.	Adjustment for nationality	To improve the power by preventing upward bias of the standard error of the outcome.
Power calculation of secondary outcomes is missing	Calculation of power conditional on sample size	To be used when defining the test ordering of the secondary outcomes
Difficulties involved in interpreting an effect on a secondary outcome that can only be measured in surviving patients was not addressed	The worst possible score is assigned to the dead patients	A surplus of patients in one group relative to the other group may die before the outcome is measured. In the other group the corresponding surviving patients may (or may not) have very poor outcomes
No multiplicity adjustment	The fixed-sequence testing procedure will be applied with the primary outcome to be tested first and followed by the secondary outcomes ordered according to falling power	To keep the family-wise error rate ≤ 0.05
A search for auxiliary variables and if found followed by imputation of the primary outcome was not considered	Missing value handling procedure revised accordingly	To improve the efficiency of a multiple imputation of missing values of the primary outcome
The analytic potential of the exploratory temperature data was not expanded on	An outline of an exploratory mixed model analyses of the temperature data and Cox analyses of time to death with censoring at end of treatment and at 91 days +/- 14 days is now included	To assess if the temperature has an impact on short-term and long-term mortality and supplement the result of the analysis of the second secondary outcome
Sample size of 1500 participants	Sample size reduced to 800 participants	Due to exceptionally slow enrolment, we realised that this target was no longer realistic

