### The interpretation of the effect on outcomes which may only be measured in surviving patients

Formally, three of the original secondary outcomes (NIHSS, EQ-5D-5 L, and infarct size) are only measurable in patients who survive until these outcomes were planned to be measured. This may make the interpretation of a significant effect on each of the last four secondary outcomes somewhat difficult when the power of detecting a small difference between the mortalities in the two groups is low. A surplus of patients in one intervention group relative to the other group may die before the outcome is measured. In the other intervention group, the corresponding surviving patients may (or may not) have very poor outcome values which may make the first group look good if the mortalities do not differ significantly.

Given the sample size of 800 patients and assuming the mortality in one group is 0.17 (e.g. in the control group, see above) the probability of not detecting an absolute reduction in mortality in the experimental group of 0.01, 0.02, 0.03, 0.04, and 0.05 is 0.93, 0.89, 0.81, 0.70, and 0.57, respectively. Thus, differences in mortality of the intervention groups of 5% or less are likely to remain undetected with a relatively high probability. Therefore, we have elected to include the dead patients in the comparison between the two intervention groups by assigning the worst possible score to the dead patients. The EQ5D5L is used to estimate QALYs gained in each arm of the trial population. QALYs are estimated by summing up the time spent in each state multiplied by the quality of life attributed to this state. By definition, the value of QALYs is zero from the time of death onwards. Total QALYs will be computed and reported for each patient for the entire duration of the follow-up.

For the study of prognostic markers in the EuroHYP-1 trial, we will apply similar principles as in the Clarithromycin in Patients with Stable Coronary Heart Disease trial (CLARICOR) trial [18]. The study of prognostic markers will not be part of the primary publication.

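### Deaths are scored at the NIHSS maximum of 42 but tested with a linear model and no rank-based alternative, which costs much of the power at the first secondary test

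*SAP article*

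**What the plan says.** Deaths: the Discussion section on outcomes measurable only in survivors settles on "assigning the worst possible score to the dead patients". The amendments table says the same: "The worst possible score is assigned to the dead patients". Table 5 gives the NIHSS range as 0 to 42, with 42 as the worst value.

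Test: under The secondary and the exploratory outcomes, the SAP specifies "the general linear univariate model for continuous outcomes, and the Poisson distribution or negative binomial distribution for rate outcomes will be used". The fallback in that section has one trigger: "If the assumptions of the Poisson or negative binomial models are not fulfilled with reasonable approximation, a non-parametric method" (van Elteren by nationality of centre) then replaces the rate model. The primary mRS has its own fallback if proportional odds is rejected: "the groups will be compared using a non-parametric method (van Elteren and stratification by nationality of centre) and the result will be the primary result". Continuous outcomes have none.

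Place in the sequence: NIHSS comes first among the secondary outcomes because its stated power is highest (1.00, Table 2). Under Multiplicity, formal testing ends at the first non-significant result.

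**The concern.** A worst score for death is a way of ordering patients: dead is worse than any living state. A linear model uses more than the order. It treats the 34 points between 42 and the assumed control mean of 8 as measured neurological deficit. With mortality near 17%, that gap can dominate the variance, so a real benefit in survivors becomes hard to detect. The estimated mean difference also becomes a blend of deficit and mortality.

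Because NIHSS is the first gate after the primary outcome, a missed effect there also ends formal testing of the five outcomes behind it: serious adverse events, death or dependency, infarct size, EQ-5D-5 L and death.

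**Working it through.** **Inputs.** From Table 2 and the section on power of the secondary outcomes: NIHSS control mean 8, SD 5, relevant difference 2, N = 800, mortality 0.17 in controls and 0.1316 with cooling. From Table 5: worst NIHSS 42. From Analytical principles: two-sided 5% tests. Assumed here: 400 per arm, mean 8 and SD 5 describe survivors, no covariate adjustment.

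**The SAP's own figure.** Standard error = 5 × √(2/400) = 0.354; 2/0.354 = 5.66; power = Φ(5.66 − 1.96) = 0.9999. This reproduces the stated 1.00, so that figure uses SD 5 without deaths at 42. SD 5 cannot already include them: the split alone gives an SD of 34 × √(0.17 × 0.83) ≈ 12.8.

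**Adding the deaths.** With mortality p, survivor mean m and SD s, and death score w:

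- mean = (1 − p)m + pw
- variance = (1 − p)s² + p(1 − p)(w − m)²

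Control arm: mean = 0.83 × 8 + 0.17 × 42 = 13.78. Variance = 0.83 × 25 + 0.1411 × 34² = 20.75 + 163.11 = 183.86, so SD = 13.56. Share due to the dead/alive split = 163.11/183.86 = 0.887.

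Cooled arm, survivors 2 points better, same mortality: mean = 0.83 × 6 + 0.17 × 42 = 12.12, a difference of 1.66. Variance = 20.75 + 0.1411 × 36² = 203.62. Average SD = √((183.86 + 203.62)/2) = 13.92. Standard error = 13.92 × √(2/400) = 0.984. Power = Φ(1.66/0.984 − 1.96) = 0.39. About 1104 per arm would be needed for 80% power.

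**Linear against rank test.** A t-test stands in for the unadjusted linear model and an unstratified Wilcoxon test for the rank method. Survivor scores were simulated as normal or gamma, with a 2-point benefit in survivors:

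| Mortality, control v cooled | Linear | Rank |
|---|---|---|
| 17% v 17% | 0.36-0.39 | 0.97-0.99 |
| 17% v 13.16% | about 0.89 | above 0.99 |
| 17% v 19% | 0.12-0.15 | 0.90-0.96 |
| 10% v 10% | 0.54-0.60 | above 0.99 |
| 5% v 5% | 0.79-0.84 | above 0.99 |

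Repeat runs move these figures by a few hundredths, depending on the survivor distribution. With no effect on either survivors or mortality, the linear test rejects in 0.047-0.048 of runs, so it is valid.

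**What the mean difference contains.** With no effect in survivors, the SAP's mortality difference alone shifts the mean by 0.0384 × 34 = 1.31 points. With both effects, the cooled mean is 0.8684 × 6 + 0.1316 × 42 = 10.74. The difference is then 3.04, of which 1.31 (43%) comes from mortality. In the other direction, a 2-point survivor benefit vanishes when 6 + 36p = 13.78, that is p = 0.216. That is (0.216 − 0.17) × 400 ≈ 18 extra deaths in the cooled arm.

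**Other outcomes.** For EQ-5D-5 L with death = 0, the SD rises only from 0.40 to 0.41, and a simulated comparison gave about 0.40 for the linear model and 0.47 for the rank test. For infarct size, Table 5 gives the worst value as 1 without a unit while the power calculation is in ml, so no figure can be derived.

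**The case against.** Five counter-arguments deserve an answer.

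- **Equal mortality is unkind to the linear model.** The SAP assumes a common odds ratio of 0.74 at every cut, including death. Under the resulting 17% v 13.16%, linear power is about 0.89. That stands and belongs beside the lower figure. The rank test is still above 0.99 there, and it is ahead in every scenario run with a survivor benefit.
- **Letting deaths count is the plan's declared aim, and the linear test is valid.** Both are true. A rank analysis also counts deaths, and also responds to mortality alone: with no survivor effect and 17% v 13.16%, it is significant in about 15% of runs, against about 29% for the linear test. The difference is one of degree.
- **The scores are not freely chosen.** NIHSS 42 is the scale maximum. For EQ-5D-5 L, zero is a meaningful utility for death and fits the SAP's QALY definition, so a mean is a defensible target there. This removes EQ-5D-5 L from the concern. For NIHSS the score is fixed, but its distance from survivors' scores is still not a measured deficit.
- **The simulations are unadjusted**, whereas the SAP adjusts for country and seven factors, including severity and age. How far adjustment narrows the gap was not examined.
- **Van Elteren by country would drop the minimisation factors** that Analytical principles requires. This stands, and it shapes the fix.

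A reader might also infer that a few deaths swamp every continuous outcome. The documents do not support that. About 120 to 136 deaths are expected, and a net difference of some 15 to 18 decides the NIHSS result. For infarct size, assumed death rates and worst volumes gave results that changed direction with the assumed distribution.

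**Conclusion.** The point holds for NIHSS and should be corrected. The SAP combines a worst-score rule for deaths with a linear model and offers no rank-based alternative for continuous outcomes. At the first secondary gate, power for a 2-point survivor benefit falls from the stated 1.00 to about 0.36-0.39 at equal mortality, and to about 0.89 with the SAP's mortality difference. A rank test keeps at least about 0.97 in both cases. If cooled mortality were slightly higher (17% v 19%), the contrast is about 0.12-0.15 against 0.90-0.96.

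This rests on mean 8 and SD 5 describing survivors, 400 per arm and no covariate adjustment. It does not show an inflated type I error, a quantified loss for infarct size or a material loss for EQ-5D-5 L. Nor does it show that van Elteren is reserved for rate outcomes throughout the plan: that is so among the secondary and exploratory outcomes only, since the mRS has its own fallback.

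**What to change.** Under The secondary and the exploratory outcomes, make the test for NIHSS a rank-based analysis with deaths tied at the worst rank, adjusted for country and the seven minimisation factors. Analysis of covariance on ranks or a proportional-odds model would serve. Keep van Elteren by country as a sensitivity analysis only. In Table 5, report deaths per arm and the linear-model mean difference with deaths at 42 as description. Restate the NIHSS power for the adopted analysis, so that the power-based test order rests on the test actually used.

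The same method may be used for infarct size. That section of the SAP on power calls the outcome exploratory yet lists it in the sequence, and no usable worst value in ml is given. No change is needed for EQ-5D-5 L on these grounds.

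Cost: SAP wording and a few lines of code before unblinding, with no new data. The P value is no longer on the mean scale and death carries less weight, but death is already a separate secondary outcome.
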